### Objectives

Primary objectives: to evaluate the safety of the antivenom including number and severity of acute adverse events, as well as deaths suspected to be related to the intervention; and to confirm the lowest effective dose when faced with different quantities of venom inoculated in patients exposed to multiple stings from Africanized honeybees.Secondary objectives: to correlate the severity of the initial clinical condition with number of stings.Explanatory objectives: to evaluate the antivenom neutralizing power by pharmacokinetic and proteomic studies; and to evaluate the antivenom pharmacokinetics and immunogenicity.

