**Fig. 1 Fig1:**
[figure not shown]
Temporal distribution of the number of cases reported for Africanized honeybee sting in Brazil between 2000 and 2015 [4]

The physiopathology of this accident is complex due to the interaction between the diverse toxic components of the venom, the potential target organs and the immune response of the victim [5, 6]. Generally, bee stings can present two different outcomes:Anaphylaxis: occurs in individuals allergic to bee venom. In these cases a single sting can cause serious generalized allergic reactions, possibly leading to death. These consequences are not related to the toxicity of the venom due to the small quantity inoculated. Treatment is limited to general measures and the use of symptomatic drugs aiming to control the anaphylaxis [7].Direct toxicity from the venom: occurs when there are a substantial number of stings – generally more than 200 in adults. In this case, the venom volume is sufficient to cause damage to vital organs. Prominent among the toxic components are melittin and phospholipase A_2_, whose presence accounts for more than 60% of the dry weight of the venom. Direct injury to the cardiovascular, muscular, neurological, dermatological, metabolic, hematological, respiratory and renal systems can lead to death [7, 8].

The clinical manifestations resulting from multiple stings are: generalized pain, intense pruritus, flushing, hyperthermia, papules, urticarial plaques, hypotension, tachycardia, headache, nausea, vomiting, abdominal colic, bronchospasms and psychomotor agitation, which may subsequently evolve to a state of torpor, accompanied by respiratory and cardiac failure and, principally, severe renal failure [8–10]. The most common laboratory alterations are: leukocytosis with neutrophilia, hemolysis, thrombocytopenia, disseminated intravascular coagulation, rhabdomyolysis with increase of creatine phosphokinase (CPK), elevation of the enzymes aspartate aminotransferase (AST) and alanine amino transferase (ALT), increase of urea, creatinine and myoglobin in the urine [8–10].

Mortality is elevated at the extremes of age [4]. In children, due to lower body mass, envenomation can be much more severe, since with many stings the concentration of the toxic components is elevated. In the elderly, greater risk involves such preexisting comorbidities as chronic renal, cardiac or respiratory failure. These constitute an important additional risk factor in patients who are victims of multiple stings.

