### Design of the *Apis* study

This is a multicenter, non-randomized and open phase I/II clinical trial study to evaluate the safety, determine the pharmacokinetic and proteomic profile, and confirm the lowest antivenom dose, according to the severity of each case. It will include 20 adult individuals, of both sexes, afflicted with multiple stings from Africanized *Apis mellifera* honeybees. The study population will be of the type non-probabilistic by convenience (or accidental) sample, given the low demographic density of the studied phenomenon and the extreme geographic decentralization of this event. The sample size was estimated by considering examples of phase I/II clinical studies proposing to study the safety and neutralizing power and to confirm the minimum required dose of antivenom [12]. Not performing the sample calculation is justified by the fact that the efficacy outcome is not the target at this moment given that there are no data on safety and adequate dose. The study will last 36 months, with 24 months for recruitment.

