### Outcomes

Primary outcomes: to evaluate the antivenom safety profile through laboratory and clinical adverse events; to verify the proportion of individuals with improvement in the initial clinical picture by monitoring signs, symptoms and laboratory exams.Secondary outcomes: to evaluate the degree de correlation between the number of stings and the severity of the initial clinical picture (APACHE II).Exploratory outcomes: to evaluate the pharmacokinetic and immunogenic profile of antivenom/venom at doses established by an analysis of the blood samples collected at different moments (before and at 2, 6, 12 and 24 h after heterologous serum therapy); to evaluate the proteomic profile of the antivenom as determined by the differential expression of the proteins albumin, C-reactive protein (CRP) and fibrinogen, by the presence of the components melittin and phospholipase A_2_, and by the heterologous serum protein profile of the degradome and peptide/protein biomarkers.

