### Plan of treatment (specific, adjuvant, symptomatic and complementary)

#### Specific treatment

The *WHO Guideline for the production control and regulation of snake antivenom immunoglobulins* [12] suggests that the protocol prepared for the specific treatment be based on the estimated quantity of venom inoculated by the bee and on the neutralizing capacity of the antivenin. Thus, the authors suggested:Up to 5 stings: specific treatment is not indicated, except for a medical criterion.Between 5 and 200 stings: two vials of apilic antivenom.Between 201 and 600 stings: six vials of apilic antivenom.Above 600 stings: ten vials of apilic antivenom.

After the dose is determined by the attending medical team, the vials must be opened and their content aspirated by means of a syringe. Next, insert all the content into a flask containing 250 mL of normal 0.9% saline solution, previously emptied. This flask containing the antivenom must be connected into a Y formation with another flask containing 250 mL of 0.9% saline. One large-caliber vein of the forearm must be catheterized and these two contents need to be infused in the Y within two hours. All patients must be hospitalized and monitored throughout the infusion by the continuous presence of the hospital staff at the patient’s bedside. The team must also have at their disposal the drugs and equipment necessary for the treatment of mild or severe adverse reactions. Any adverse events and signs and symptoms of possible toxicity must be noted on the patient’s chart.

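### The primary objective of confirming the lowest effective dose is out of reach: each sting band has one listed dose, so the trial can at most describe whether that dose looks adequate

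*Protocol article*

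**What the plan says.** All references are to the Protocol article.

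- **Objectives** (primary): besides safety, "to confirm the lowest effective dose when faced with different quantities of venom inoculated in patients exposed to multiple stings". The Abstract (Methods), the end of the Background and Design of the Apis study state the same aim in similar terms, as confirming or standardizing the lowest dose.
- **Design of the Apis study**: "This is a multicenter, non-randomized and open phase I/II clinical trial study to evaluate the safety". It has 20 participants and no sample-size calculation, on the ground that "the efficacy outcome is not the target at this moment given that there are no data on safety and adequate dose".
- **Specific treatment**: "Between 5 and 200 stings: two vials of apilic antivenom"; "Between 201 and 600 stings: six vials of apilic antivenom"; "Above 600 stings: ten vials of apilic antivenom". The later sections on conduct by number of stings repeat these doses, with and without anaphylactic shock.
- **Outcomes** (primary, beside safety): "to verify the proportion of individuals with improvement in the initial clinical picture by monitoring signs, symptoms and laboratory exams". The secondary outcome is the correlation of sting number with initial severity (APACHE II). Venom and antivenom kinetics, sampled before and at 2, 6, 12 and 24 h after treatment, are exploratory.
- **Adjuvant treatment** and **Symptomatic treatment**: fluids, vasoactive drugs, antihistamine, corticosteroid and bronchodilators may be given alongside the antivenom.

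**The concern.** To call a dose the lowest effective one, the trial must show what a smaller dose does at a similar venom load. The listed rule never plans that. A patient with a given sting count has one listed dose, and patients on different listed doses differ in sting count. The secondary objective is to correlate sting count with severity, so the article itself treats the variable that fixes the dose as a likely marker of severity.

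The primary improvement outcome does not fill the gap. It has no comparator, and patients receive supportive care at the same time. The Background (text after Fig. 1) puts direct venom toxicity at "generally more than 200 in adults", and the two-vial band lies wholly at or below that count. Improvement there is especially hard to credit to the antivenom.

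At stake is what the trial may conclude. The article expects its results to support later studies. A report that the lowest effective dose had been confirmed would pass on as established a dose that was never compared with a smaller one.

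**Working it through.** **1. The plan's own figures.** The sample size of 20 cannot be reproduced, because the article says no calculation was made. The dose arithmetic in Antivenom development and dose proposal can be checked. Its inputs are 0.1 mg of venom per sting and 1.25 mg neutralized per mL:

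10 mL × 1.25 mg/mL ÷ 0.1 mg per sting = 125 stings.

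The article states 100 stings per 10 mL. It does not say whether the gap is rounding or a margin, so the figures should be reconciled. Both values are carried below, and the conclusion is the same under each.

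**2. Nominal capacity over venom load.** Assumption: one vial holds 10 mL (the volume is not stated).

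Ratio = vials × stings neutralized per vial ÷ sting count.

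| Stings | Vials | Ratio at 100 per vial (as stated) | Ratio at 125 per vial (from the inputs) |
|---|---|---|---|
| 6 | 2 | 200/6 = 33.3 | 250/6 = 41.7 |
| 200 | 2 | 200/200 = 1.00 | 250/200 = 1.25 |
| 201 | 6 | 600/201 = 2.99 | 750/201 = 3.73 |
| 600 | 6 | 600/600 = 1.00 | 750/600 = 1.25 |
| 601 | 10 | 1000/601 = 1.66 | 1250/601 = 2.08 |

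The ratio varies widely, but within a band it varies only through sting count. At any one count it has a single planned value. It falls below 1 only above 1,000 stings (100 per vial) or 1,250 stings (125 per vial). Under the listed rule, a nominally insufficient dose would be seen only at the extreme of exposure.

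**3. What each comparison can show.**

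- *Within a band*: one dose, so no dose contrast.
- *Between bands*: dose and sting count change together, so the contrast is confounded with severity.
- *Against no antivenom*: no such group.

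None of these depends on the number enrolled. A larger trial under the same rule would have the same gap.

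**4. Sections set side by side.** Design of the Apis study excuses the missing sample-size calculation because efficacy is not yet the target. Objectives and Outcomes make an effective dose and clinical improvement primary. These statements cannot all stand.

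**The case against.** Four arguments deserve an answer.

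*Confirm may mean something modest.* The dose comes from preclinical neutralization. With 10 mL vials and 100 stings per 10 mL, two and six vials match 200 and 600 stings exactly, the nominal minimum at the top of each band. Checking that a calculated minimum looks adequate is a fair phase I/II aim, and the article elsewhere speaks of preliminary efficacy. This stands as a description of what the trial can do. It does not rescue the word lowest, which needs evidence about less.

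*Some dose variation exists.* Nearly equal loads at 200 and 201 stings get two and six vials, so it would be too strong to say that every conceivable dose contrast is purely one of severity. But no comparison at the boundary is planned, 20 participants would put few there, and both doses are nominally sufficient.

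*The rule may be less rigid than it looks.* The bands are presented as suggestions, the attending team settles the dose, and a full protocol may say more. This is fair as far as it goes: the article does not prove that no participant will ever receive a different dose. But unplanned departures chosen by clinicians are not a designed contrast, and the article describes no other.

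*Efficacy is measured elsewhere.* A reader might infer that improvement is the only efficacy measure. The documents do not support that. Neutralizing power and venom and antivenom kinetics are listed as exploratory, and Subsidiary laboratory tests links the assay to judging efficacy. These data could support adequacy of the dose given, though not that it is the lowest.

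**Conclusion.** The point holds as a mismatch between a primary objective and the treatment rule. With one listed dose per band and no control, the trial can describe whether the proposed dose looks adequate. It cannot establish that the dose is the lowest effective one or that improvement is due to the antivenom. The conflict between the design section and the primary objective and outcome is plain on the text. The safety objective is unaffected.

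The conclusion rests on the listed dosing rule. The vial volume is an assumption that affects only the illustrative ratios.

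Three stronger inferences should not be drawn:

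- That the fault is the sample size. The gap would remain at any size.
- That the Background's rates of mild disease and death predict the course of these 20 patients. Those rates cover all reported bee stings, and the article says they do not separate single from multiple stings.
- That the plan will compare bands misleadingly. Statistical analysis names general tests and specifies no contrast between bands or doses.

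**What to change.** 1. In the Abstract (Methods), Background, Design of the Apis study and Objectives, replace the aim of confirming or standardizing the lowest (effective) dose with: *describe safety, preliminary activity and clinical course at the proposed sting-banded dose*.
2. Reconcile the statement that efficacy is not the target with the primary objective and the primary improvement outcome.
3. Report improvement descriptively by sting band with exact intervals. These will be wide: with about seven participants in a band (an assumed split), 7/7 gives 59% to 100% and 6/7 gives 42% to 99.6%.
4. State that contrasts between bands are confounded with severity, and draw no conclusion about the lowest dose or about attribution to the antivenom.
5. Use the kinetics already planned at baseline and at 2, 6, 12 and 24 h as descriptive supporting evidence of neutralization. Do not presume an assay of free venom: the text describes ELISA kinetics of venom and antivenom without saying that free and bound venom are separated, and the Table 1 footnote to the pharmacokinetic profile describes IgG and IgM antibodies.

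The cost is rewording and a descriptive presentation of data already planned, with no added patients or samples. The downside is a more modest claim. No dose is proposed here.

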**Methods:**

In order to evaluate the safety and neutralizing capacity of a new apilic antivenom, as well as to confirm its lowest effective dose, a clinical protocol was developed to be applied in a multicenter, non-randomized and open phase I/II clinical trial. Twenty participants with more than five stings, aged more than 18 years, of both sexes, who have not previously received the heterologous serum against bee stings, will be included for 24 months. The proposed dose was based on the antivenom neutralizing capacity and the number of stings. Treatment will be administered only in a hospital environment and the participants will be evaluated for a period up to 30 days after discharge for clinical and laboratory follow-up.

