Complementing the results of the laboratory exams, a proteomic evaluation will also be performed by degradome analysis, seeking to evidence eventual biomarkers responsible for physiological and clinical alterations [16, 17]. Furthermore, a pharmacokinetic profile of venom and of a new antivenom will be performed utilizing immunoenzymatic methods (ELISA) due to their sensitivity, reproducibility, ease of execution and low cost. Thus, the trial denominated “venenomia” will have the objective of determining the kinetics of circulating toxins and antivenom, aiding in the diagnosis, in the determination of accident severity and in the evaluation of heterologous serum therapy efficacy [18–20].

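### Before/after toxin kinetics and host proteins in treated patients alone can describe, but cannot show, neutralization by the antivenom

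*Protocol article*

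**What the plan says.** The abstract (Methods) states that the trial is meant to "evaluate the safety and neutralizing capacity of a new apilic antivenom". In Objectives, the third tier (printed as explanatory there and as exploratory in Outcomes) is "to evaluate the antivenom neutralizing power by pharmacokinetic and proteomic studies".

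Outcomes gives the material for that judgement. Blood is taken "before and at 2, 6, 12 and 24 h after heterologous serum therapy", and the proteomic profile is determined by, among other items, "differential expression of the proteins albumin, C-reactive protein (CRP) and fibrinogen, by the presence of the components melittin and phospholipase A_2". The section on subsidiary laboratory tests adds an ELISA-based venom and antivenom profile with this stated purpose: "determining the kinetics of circulating toxins and antivenom, aiding in the diagnosis, in the determination of accident severity and in the evaluation of heterologous serum"; the sentence ends by naming the efficacy of that treatment. Table 1 continues the pharmacokinetic and proteomic profiles to day 2, discharge and the three return visits.

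On design: "This is a multicenter, non-randomized and open phase I/II clinical trial study". "It will include 20 adult individuals, of both sexes". The plan of treatment and the conduct sections give antivenom to every band above five stings: two, six or ten vials, rising with the sting count. The same design section disclaims efficacy: "Not performing the sample calculation is justified by the fact that the efficacy outcome is not the target at this moment".

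**The concern.** To attribute a fall in circulating toxin to the antivenom, one must know how far the level would have fallen without it. The article supplies nothing that answers this. There is no untreated participant in the study population. The dose bands cannot stand in for one, because dose is set by venom load. A single pre-infusion sample gives no pre-treatment trend. No external kinetics are cited as a reference, and neither Outcomes nor the laboratory section says that free venom will be distinguished from antivenom-bound venom.

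The comparison can mislead in both directions. Toxin is eventually cleared even if the antivenom binds nothing, so an inert product can look active. If venom is still being absorbed from the stings, levels may rise after infusion and hide real neutralization.

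The host proteins add no independent evidence. Albumin, CRP and fibrinogen respond to the illness, and the protocol's own vigorous saline (adjuvant treatment) and hydrocortisone (symptomatic treatment) may move them either way.

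At stake is a statement about neutralizing capacity that the abstract's conclusions would carry forward as support for later studies.

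**Working it through.** **The plan's own figure.** The sample size of 20 rests on other phase I/II studies, with no calculation, so there is nothing to reproduce. The article gives no alpha, effect size, variability, toxin half-life or decision rule for neutralizing power.

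**Inputs.** From the article: n = 20; sampling before and at 2, 6, 12 and 24 h; infusion within two hours; two thirds of bee-sting patients reaching hospital in under three hours. Assumed, because the article gives none: first-order clearance with half-life 2 to 72 h; SD of the individual log change 1.0 to 2.0; a paired t test at two-sided 5%, counting only rejections in the direction of a fall.

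**Formula.** With an antivenom that does nothing, the mean log fall at time t is μ = ln 2 × t / half-life. The noncentrality is (μ / SD) × √20. The test is positive when t exceeds 2.093 (19 df).

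**Example.** Half-life 12 h, t = 24 h: μ = 0.693 × 24 / 12 = 1.386. With SD 1.5, noncentrality = 1.386 / 1.5 × 4.472 = 4.13, and the chance of a positive test is 0.975. With SD 1.0, noncentrality is 6.20 and the chance is 1.00.

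| Sample | Half-life | SD | Chance an inert product shows a significant fall |
|---|---|---|---|
| 24 h | 6 h | 1.0 | 1.00 |
| 24 h | 12 h | 1.0 | 1.00 |
| 24 h | 12 h | 1.5 | 0.975 |
| 24 h | 12 h | 2.0 | 0.84 |
| 24 h | 24 h | 1.0 | 0.84 |
| 24 h | 36 h | 1.0 | 0.50 |
| 24 h | 48 h | 1.0 | 0.31 |
| 24 h | 72 h | 1.0 | 0.16 |
| 2 h | 2 h | 1.0 | 0.84 |
| 2 h | 6 h | 1.0 | 0.16 |
| 2 h | 12 h | 1.0 | 0.07 |

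**Continuing absorption.** Add a first-order depot, with baseline 3 h after the stings, a 2 h infusion and SD 1. At 24 h the chance is 0.98 for absorption half-life 2 h with elimination 12 h, 0.20 for 2 h with 24 h, and 0.01 for 6 h with 12 h. In the last case the expected level is still above baseline (log change +0.13).

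**With a valid reference.** A two-sample test against untreated kinetics (20 v 20 or 10 v 10, half-life 12 h, SD 1) calls an inert product neutralizing in about 2.5 to 3% of trials. The excess comes from the missing reference.

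**Can each participant's own pre-infusion trend replace the reference?** Suppose an arrival sample is taken 1 h before the pre-infusion sample and the slope is extrapolated 2 h forward. If the infusion takes 2 h and the sample is 2 h after it, the true gap is 4 h. With half-life 3 h and assay CV 20%, an inert product is then called neutralizing in about 79% of trials. With absorption half-life 2 h, elimination 12 h and CV 20%, the rate runs from about 13% (arrival 3 h after the stings) to 97% (arrival 1 h). This rule is biased toward false positives and is not a remedy.

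**Host proteins.** No number applies. The treatment sections and the outcome list together show that the direction of change cannot be assigned to venom neutralization.

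**The case against.** The strongest reply is that the article never commits to the test simulated here. Its statistical section names only chi-square, Fisher, Student's t and Mann–Whitney tests for comparison among participants. Outcomes speaks of a profile, and the laboratory section of kinetics aiding evaluation alongside diagnosis and severity. Neutralizing power is in the lowest tier, and the design section says efficacy is not the target. The ELISA's target, free or total venom, is a detail that an article may leave to the full protocol. Antivenom is measured too, and Table 1 extends the profile well beyond 24 h.

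Most of this stands and limits the size of the point. A reader might infer that natural clearance would pass for neutralization in almost every such trial. The documents do not support that: half-life, variability, time point and decision rule are all assumed, and the computed rate ranges from about 1% to 100%. Nor can it be said that no kinetic measure could ever tell an active antivenom from an inert one, since a free-versus-bound assay might. And the host proteins are confounded; they are not certain to look like neutralization.

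What does not stand is that the lower tier settles the matter. The article disclaims efficacy in one section, yet uses kinetics to help evaluate efficacy in another and puts neutralizing capacity in the abstract's statement of purpose. Later samples in treated patients and antivenom levels do not supply the natural course of the venom, and no analysis plan can recover a comparator that the design does not collect or name.

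**Conclusion.** The point holds as a limit on interpretation. With all participants treated, dose tied to sting count, one pre-infusion sample and no named reference, before/after toxin change is not evidence of neutralization or efficacy. This follows from the design and needs no simulation.

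The size depends on assumptions outside the article. About 97% or more of trials of an inert product would be positive on a 24 h before/after test with 20 participants if clearance is first order, the half-life is at most about 12 h and the log-change SD is 1 to 1.5. The figure drops sharply outside those conditions, and the article states no such test. Because the objective is exploratory and efficacy is disclaimed, this is a correction that should be made to the claims; it is not a flaw in the primary analysis.

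**What to change.** Align the abstract's Methods, Objectives, Outcomes and the text on subsidiary laboratory tests:

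- State that venom and antivenom kinetics are descriptive, and that before/after change in treated participants is not evidence of neutralization or efficacy.
- Do not count albumin, CRP and fibrinogen as neutralization evidence; keep them as safety and severity descriptors.
- Reword the aim as describing venom and antivenom kinetics, unless a valid reference is named: external kinetics in untreated patients, or an assay separating free from antivenom-bound venom.
- Do not substitute an extrapolation of each participant's own pre-infusion slope, for the reasons shown in the check.

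The wording changes need no extra sample, assay or participant. Their cost is a less favourable claim. Naming a reference would add the work of obtaining it.
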